**Figure 1. f1:**
[figure not shown]
Trial design and flow diagram.

**Figure 2. f2:**
[figure not shown]
Estimated power based on the two simulation studies.

A baseline chest radiograph will be performed. A CT or MRI brain scan will be performed if there is evidence of raised intracranial pressure or focal neurological abnormalities according to local practice and resources.

### Hospital admission

Intravenous amphotericin B is administered for 14 days necessitating hospital admission during this period. Study treatment and antifungals will be directly administered during this time period.

### Clinical monitoring

Patients will have daily Glasgow Coma Score and review as per standard care until discharge from hospital. The decision to discharge patients from the hospital is at the attending physician’s discretion and is based upon the clinical status of the patient. Following discharge patients will be seen weekly until 4 weeks, at 6 weeks and at 10 weeks. If the exact visit day is not feasible, scheduled visits can occur at up to 5 days following the stipulated time to account for weekends and holidays (for example, the 4 week review should occur at on day 28–33 following randomisation, week 10 visit on day 70–75). Patients will be monitored closely for

Death - the date of death and cause will be recordedNew neurological events (onset of new focal neurological signs or fall in Glasgow coma score of ≥ 2 points for ≥ 2 days, following > 7 days clinical stability or improvement after randomization)Drug-related adverse eventsNew or recurrent AIDS defining illnessesVisual deficit (at week 10)IRISRaised intracranial pressure (clinical or measured)

Uniform management of patients and recording of data will be ensured by the local study staff who will do clinical assessments daily while admitted and at follow-up visits. Uniform management and data recording will be ensured through training of study staff, standard operating procedures for the administration of drugs and identification and management of specific complications, and the use of a clinical reporting form that has been developed in previous OUCRU studies. The study has a follow-up period of 10 weeks post-randomisation, and the full study analysis will be performed and the data submitted for publication when the last patient under follow-up has reached this timepoint.

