## Other effects

An early trial of high dose Tamoxifen (equivalent to >450mg/day) in patients with epithelial tumours reported a sense of light-headedness and unsteady gait in a proportion of patients, which resolved within 2–5 days of stopping the drug
^26^. Tamoxifen does not have any expected haematological or hepatic side effects.

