***Visual deficit at 10 weeks.*** Visual deficit occurs in 5–40% of patients with cryptococcal meningitis depending upon underlying immune status
^5,
8^. The pathogenesis is unclear. We will compare the incidence of blindness and other visual deficit between treatment groups. Visual deficit will be assessed using a simple 6 point scale, as used in previous studies (see
Table 3).

***Time to new neurological event or death until 10 weeks.*** A neurological event is defined as a fall in Glasgow coma score by ≥2 points for ≥2 days from the highest previously recorded Glasgow coma score (including baseline) or the occurrence of any of the following adverse events: cerebellar symptoms, coma, hemiplegia, paraplegia, seizures, cerebral herniation, new onset blindness or deafness, or cranial nerve palsy.

***Longitudinal measurements of intracranial pressure during the first 2 weeks.*** Intracranial pressure (ICP) will be measured at study entry, day 3, 7, and 14, and if clinically indicated (depending on local practice). The main outcomes are longitudinal ICP-measurements until day 14.

Clinical need and local practice will determine the frequency of lumbar punctures post day 14 and clinician’s diagnoses of raised ICP based upon the presence of headache, nausea, diurnal and postural variation, relief with lumbar puncture and presence of papilloedema. Thus, these measures will only be descriptively analyzed.

***CD4 count at 10 weeks.*** CD4 count measurement is indicated in HIV infected patients, and CD4 lymphopenia has been described in HIV uninfected patients with cryptococcal meningitis. Moreover, Tamoxifen may reduce CD4 cell apoptosis which may be beneficial
^47^.

***Blood and CSF concentrations of amphotericin, Tamoxifen and fluconazole.*** Pharmacological data on antifungal drugs are lacking. Dosing has been inferred from studies in healthy volunteers, or patients with other diseases. There are no studies of combination therapy at the doses currently recommended
^48–

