## Recording and reporting of Adverse Events and protocol violations

### Adverse event recording

Grade 3 and 4 adverse events will be
**recorded** in the case report form and entered to the study database. Grade 1 & 2 events will not be recorded since in a severe disease such as cryptococcal meningitis the number of low grade adverse events is likely to be high representing a large reporting burden which may impact upon the quality of recording and reporting of more important grade 3 and 4 adverse events.

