### Analysis of other secondary outcomes

The rate of IRIS and the rate of relapse (defined as antifungal treatment intensification or re-treatment) will be modeled with cause-specific proportional hazards models with treatment as the only covariate and stratification by HIV infection status.

The visual acuity at 10 weeks is recorded on a 6 point scale and will be summarized by treatment arm for each eye separately, and overall where “overall” is defined as the worst recorded acuity of either eye. The odds of having “normal acuity” (amongst all surviving patients with a visual assessment) will be informally compared between the treatment arms with a logistic regression model adjusted for HIV status.

The time to the first new neurological event or death until 10 weeks will be analyzed in the same way as overall survival. Longitudinal measurements of intracranial pressure during the first 2 weeks will be modeled using a mixed effect model as described for the primary outcome. CD4 cell count at baseline and 10 weeks will be summarized and the change compared between the two groups based on a linear regression model with treatment as the main covariate and adjustment for HIV status and baseline CD4 cell count.

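### Two incompatible definitions of a new neurological event; under the monitoring one, no GCS-based event can start in the first week

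*Protocol article*

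**What the plan says.** The article describes the event in two places and uses it in a third.

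- **Secondary endpoints** (time to new neurological event or death until 10 weeks) gives the formal definition. The GCS limb is a "fall in Glasgow coma score by ≥2 points for ≥2 days from the highest previously recorded Glasgow coma score (including baseline". The other limb is any adverse event from a closed list: "cerebellar symptoms, coma, hemiplegia, paraplegia, seizures, cerebral herniation, new onset blindness or deafness, or cranial nerve palsy". Neither limb has a waiting period.
- **Clinical monitoring** lists what staff must watch for and includes an item of the same name. It is described as "onset of new focal neurological signs" or a "fall in Glasgow coma score of ≥ 2 points for ≥ 2 days, following > 7 days clinical stability or improvement after randomization".
- **Analysis of other secondary outcomes** states: "The time to the first new neurological event or death until 10 weeks will be analyzed in the same way as overall survival". It does not repeat a definition or point to one.

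On data collection, Clinical monitoring says: "Patients will have daily Glasgow Coma Score and review as per standard care until discharge from hospital". The footnote to Table 2 also has GCS assessed daily for in-patients. The Hospital admission section says the 14 days of intravenous amphotericin require a hospital stay.

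**The concern.** The two texts use the same name and the same size and duration of GCS fall, so each looks like the definition of the endpoint event. They would classify the same patient differently. Naming baseline as a possible reference score shows that the endpoint definition means early falls to count. The monitoring wording rules them out.

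What is at stake is a time-to-event secondary outcome. If the monitoring wording feeds the analysis, the GCS component has a built-in blank first week. That week lies in the induction phase, when the randomised drug is given and when an early benefit or an early toxic effect could first show. The trial is also open-label, so the choice between two definitions should not still be open once outcome data can be seen.

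**Working it through.** The plan gives no sample size, power or alpha for this endpoint, so there is no figure to reproduce. The check is a comparison of the texts and a count of days, taking day 1 as the day of randomisation.

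**Side by side**

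| Element | Secondary endpoints | Clinical monitoring |
|---|---|---|
| Size and duration of GCS fall | ≥2 points for ≥2 days | ≥2 points for ≥2 days |
| Reference score | Highest earlier score, baseline included | Not stated |
| Condition before the fall | None | >7 days of stability or improvement after randomisation |
| Other qualifying events | Closed list, including seizures, coma and herniation | New focal signs |

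The texts differ in three of the four rows. It is unclear whether the >7-day condition in the monitoring text also covers focal signs, so the count below is for the GCS limb only.

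**Earliest possible GCS event**

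- Endpoint definition: baseline is a valid reference, so a fall can begin on day 1–2 and is confirmed on about day 3–4, once it has lasted 2 days.
- Monitoring definition: more than 7 days must pass first. The earliest onset is day 8 if elapsed time is counted, or day 9 if 8 full calendar days are required. No onset in days 1–7 can qualify on either count.

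**Share of the relevant periods**

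- Tamoxifen period (days 1–14): 7/14 = 50%.
- Follow-up (to day 70): 7/70 = 10%.

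**One patient under both rules.** Take GCS 15 at baseline and 12 on days 3, 4 and 5. The fall is 15 − 12 = 3 points for 3 days.

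- Endpoint definition: 3 ≥ 2 points and 3 ≥ 2 days, so this is an event with onset on day 3.
- Monitoring definition: fewer than 7 days have passed since randomisation, so it is not an event.

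**Patients with no stable spell.** Under the monitoring text, a patient who never has more than 7 days of stability or improvement cannot meet the GCS limb at any time up to week 10.

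**Alternative parsing.** The monitoring phrase could be read as either more than 7 days of stability, or improvement of any length after randomisation. That would admit a first-week fall after early improvement. It would still exclude a first-week fall straight from baseline, as in the patient above, so the conflict remains.

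**The case against.** The strongest reply is that the endpoint has only one formal definition. It stands under Secondary endpoints, is worded as a definition and matches the outcome that is analysed. The Clinical monitoring text is a watch list. Nothing shown says that endpoint events are taken from that list, and the case report form and operating procedures are not available. With daily GCS in hospital, the formal GCS limb can be rebuilt from raw scores. All of this stands, and it makes the harm conditional on the data source. It does not remove the contradiction: the same name carries two rules, and no text says which one prevails.

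A reader might infer more than the documents support:

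- **That low-grade neurological events are wrongly lost.** The Adverse event recording section does say "Grade 1 & 2 events will not be recorded", but this is a deliberate choice with a stated reason. Counting only listed events recorded at grade 3–4 is consistent with it. The gait problem that an early high-dose study "reported a sense of light-headedness and unsteady gait in a proportion of patients" concerned doses equivalent to more than 450 mg/day, against 300 mg/day here, and the protocol does not call it cerebellar.
- **That at least half of all days with daily GCS are blocked.** The stay is at least 14 days, so days 1–7 make up at most half of it. For a 21-day stay the share is 7/21 = 33%.
- **That patients who worsen from entry can qualify only by dying, so that the composite mostly repeats survival.** Under the endpoint definition they qualify from the start, and coma, seizures, hemiplegia and herniation count without any delay. Even the monitoring text has its focal-sign limb. No figure in the protocol shows how far the composite follows survival.

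**Conclusion.** The contradiction is real and the documents do not resolve it. The definitions differ on the >7-day condition, the reference score and the non-GCS events. If site-declared events under the monitoring wording are analysed, the GCS limb cannot register an onset in days 1–7, and it can never register one in patients without a stable or improving spell of more than 7 days. If the GCS limb is derived from daily scores under the formal definition, this loss does not occur. Which route is used cannot be told from the article.

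The conclusion assumes that day 1 is the day of randomisation and that the monitoring clause is read plainly. It is limited to GCS-based events and to one secondary endpoint of a 50-patient phase II trial. EFA, its power and overall survival are not affected.

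**What to change.** 1. State in Analysis of other secondary outcomes that the Secondary endpoints definition governs the time to first new neurological event or death.
2. Remove the >7-day condition from the Clinical monitoring item and align its wording with the endpoint definition, including the reference score and the list of other events.
3. Derive the GCS component from the daily in-patient scores by a fixed rule (≥2 points below the highest earlier score, baseline included, for ≥2 days) and not from site-declared events. The 14-day admission means that these records cover the whole tamoxifen period for patients who stay in hospital as planned.

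The cost is a few sentences and a short derivation from data already collected. The Trial status section says that enrolment has finished and analysis is ongoing, so steps 1 and 3 carry the practical weight. They should be settled before outcomes are compared by arm. New prospective capture of low-grade events is no longer possible and is not part of this fix.

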### Adherence monitoring

All administration of study and antifungal drugs will be directly observed and recorded in the treatment medication sheet of the CRF during the in-patient stay. On discharge, sufficient fluconazole will be dispensed to meet the patient’s needs until 10 weeks following randomization, plus 3 extra days. At each study visit a pill count will be performed to monitor adherence to antifungal therapy.

### Cardiac monitoring

ECGs (50mm/sec) will be performed twice daily immediately before and 2 hours after administration of Tamoxifen during the first 14 days, and on days 21 and 28. ECGs can be repeated more frequently according to the patient’s needs. The QTc will be calculated as described in section ’Prolongation of the QT Interval’.

*Laboratory monitoring*

## Blood

Inpatient laboratory monitoring will be as shown in the study schedule (
Table 2). Patients will have daily monitoring of potassium and alternate day monitoring of creatinine, calcium and magnesium levels for the first 2 weeks of the study(i.e. days 1, 3, 5, 7, 9, 11, and 14. Following this point levels will be monitored as clinically indicated. Full blood count will be measured at study entry, and at days 7 and 14, and thereafter as clinically indicated. CD4 count will be measured in all patients during week 1 and at day 70.

## Cerebrospinal fluid

Lumbar puncture will be performed on days 1, 3, 7 and 14 following randomization. CSF opening and closing pressure will be measured on each sampling. Following the initial diagnostic lumbar puncture, routine diagnostic investigations will be performed according to clinical need. Whenever CSF is sampled, the fungal burden will be determined by culture (0.5mL), an aliquot immediately processed and frozen to -80°C for subsequent drug level measurement (1-1.5mL), and the remainder of any CSF (ie above that needed for clinical care and the PK measurements, and between 1-40mls, depending upon the amount needed to be removed to manage the CSF pressure) immediately processed for RNA extraction for gene expression studies. Rarely (approximately 0.5%) TB meningitis can occur at the same time as cryptococcal meningitis. Patients should have CSF tested by GeneXpert or smear or other nucleic acid amplification test during the first week of study treatment.

## PK sampling

### Plasma sampling for PK

Participation in the plasma PK study will require additional consent from the patient. Patients who agree to participate will have baseline bloods taken prior to medication being given, but amphotericin will be prepared, ready for administration, so that the infusion can commence without delay following venesection. 1.5ml of blood will be taken in a plain tube and transported in iced water to the laboratory where it will be immediately centrifuged and the plasma frozen to -80°C for storage. This will be the 0hr sample. The standard 4 hour amphotericin infusion will then commence, and oral fluconazole and Tamoxifen will be administered. Patients will be sampled for PK a total of 5 times each on day 1 and day 7. The total volume of blood drawn will be 7.5mL on each day. The exact timing of blood draws is currently being modelled based on previous Vietnamese data by [name] in Liverpool, such that the most efficient sampling schedule is used. The timing of administration of all antifungal drugs will be meticulously recorded. In addition, every time a lumbar puncture is performed, a paired plasma sample will be taken (1.5mL).

### CSF sampling for PK

PK CSF sampling will not require additional lumbar punctures (see section ’Clinical Monitoring’, subsection ‘Cerebrospinal fluid’). Rather, the timing of all lumbar punctures will be meticulously recorded along with the timing of antifungal drug administration. 1-1.5ml of CSF will be required for PK studies. PK studies will only be done if there is sufficient sample available after routine clinically indicated investigations have been performed. Every time a lumbar puncture is performed, a paired plasma sample (1.5mL) will be taken for drug concentration determination (see section ‘Laboratory Monitoring’, subsection ‘PK Sampling’).

## Other investigations

Other investigations may be performed as clinically indicated. Data for the following will be recorded when performed for routine clinical care:

CSF, if neurological deterioration (Gram stain and routine culture, ZN stain and mycobacterial culture, India ink stain and fungal quantitative culture)Sputum, if symptomatic (routine culture, ZN stain)Urine culture, if urinary symptoms (urine culture)Stool culture, if prolonged diarrhoea (microscopy, culture and parasites)Blood cultures, if persistent feverLymph node aspiration (routine and mycobacterial cultures)Blood glucose will be measured when CSF is examined or if hyper or hypoglycaemia is suspectedLiver function tests

A window period of +/- 2 days outside of the scheduled laboratory tests will apply to all tests except for electrolytes including potassium, magnesium and calcium, and those needed at baseline for inclusion/exclusion criteria.

### Evaluation of Cryptococcus isolates

All
*Cryptococcus* isolates will be speciated using classical mycological and molecular methods, and typed through genome sequencing and phenotypic testing. All isolates will undergo susceptibility testing for antifungal drugs and Tamoxifen. Isolates will be securely stored in OUCRU, HTD.

### Imaging

A chest X-ray will be performed on study entry if it has not been done at the time of diagnosis. The result will be recorded in the CRF. Brain imaging is not mandated by the study. The decision to perform brain imaging will be according to local practice. Results of brain imaging when available will be recorded. The brain imaging modality of choice will be MRI.

*Other treatment*

## Antifungal treatment

All patients – control and intervention arm - will receive antifungal treatment consisting of 2 weeks of intravenous amphotericin B 1mg/kg/day combined with high dose fluconazole (800mg once daily), followed by fluconazole 800mg once daily for 8 weeks (10 weeks in total). This is locally feasible and consistent with recent guidelines
^6,
7^. Amphotericin will be administered according to recommended guidelines (see extended data, appendix 2
^58^). Following the 10 week period of therapy, HIV infected patients, provided they have responded to treatment, will receive long term secondary prophylaxis with fluconazole 200mg/day as per standard of care
^7^. For HIV uninfected patients, the dose of antifungal therapy after 10 weeks will be determined on a case by case basis depending on response to treatment and the attending physician’s judgement regarding the likelihood of there being some other chronic immunosuppressive condition. After the initial 2 weeks of the study, modification of antifungal therapy for any patient can be made according to the patient’s needs and the judgment of the attending physician. Any changes to antifungal therapy will be recorded in the case record form. The cost of antifungal treatment until 10 weeks following randomization will be covered by existing local financial support or trial finances. Following the final follow-up visit patients will continue in care under the existing local services.

## Antiretroviral therapy

All HIV infected patients will be referred to local HIV services as soon as practicable, preferably while still admitted to hospital, to ensure that they have access to locally available HIV services including counseling and ARVs.

The recent COAT trial suggests that early (within 5 weeks of diagnosis and institution of effective antifungal therapy) introduction of ARVs is associated with worse outcomes. Therefore the study protocol recommends that ARVs are begun at least 5 weeks after institution of antifungal treatment, provided the patient has made a good response. The date that ARVs are started (or stopped) in patients in the study will be recorded. Where a patient is already receiving ARVs at the time of diagnosis, the decision to continue them will depend upon the decision of the local attending physician who will make a judgement regarding whether the cryptococcal meningitis represents antiretroviral failure or not.

## Opportunistic infection (OI) prophylaxis for immunosuppressed patients

HIV infected patients will be profoundly immunosuppressed and will receive prophylactic therapy against pneumocystis pneumonia with daily trimethoprim-sulfamethoxazole, in accordance with local guidelines and practices. If other patients with non-HIV related immunosuppression are identified, then they will receive OI prophylaxis according to the local physicians’ judgement.

### Data on concomitant medications

At each visit, information on other medications, including start dates and reason for taking them, will be documented in the case record forms. 

## Management and prevention of potential cardiac adverse events

Possible side effects of Tamoxifen are described earlier.

### Electrolyte disturbances and raised creatinine

Electrolyte disturbances are common in cryptococcal disease, usually precipitated by amphotericin treatment. The likelihood of such disturbances are mitigated by pre-emptive electrolyte replacement, sodium loading, and ensuring adequate hydration. It is routine practice to administer 2 litres of normal saline and 80mmol/L of potassium chloride daily to patients receiving amphotericin treatment. All patients in the study will receive such pre-emptive fluid and electrolyte replacement unless they are fluid overloaded or have elevated serum potassium concentrations. In the event of the serum creatinine being greater than 300umol/L, the next amphotericin dose will be missed, and the hydration status of the patient re-assessed and corrected. Amphotericin will be restarted when the serum creatinine is <200umol/L.

